# **Investigational Product Information**

## **Investigational Product**

### **Name, Content, etc.**

Salvaged RBC transfusion（Cell Saver Elite, Hemonetics）

### **Packaging and Labeling**

The salvaged RBC is contained in a dedicated bag attached to the Cell Saver Elite device.

### **Quality Control**

The collected blood should be administered within 4 hours after recovery process is completed.

### **Flow from Blood Collection to Transfusion**

1. Following the instructions in the user manual, disposable components and other necessary parts are attached to the autotransfusion device.
2. The aspiration line bag is opened aseptically, and the sterilized circuit wrapped in sterilization paper is passed to the surgical field.
3. The aspiration line is received from the surgical field and aseptically connected to the reservoir.
4. The suction pressure is set. To prevent hemolysis, the suction pressure should be set to a maximum of -150 mmHg; however, in cases of rapid bleeding, the suction pressure may be temporarily increased to 250 mmHg.
5. The reservoir is primed with heparinized saline (15,000 units of heparin in 500 mL of saline solution).
6. The amount of heparinized saline dripping into the aspiration line is adjusted according to the amount of bleeding. Typically, 15 mL of heparinized saline is added to every 100 mL of collected blood.
7. Bleeding from the surgical field is aspirated using the Cell Saver Elite device. During CPB (after the ACT exceeds 200 s and before protamine is administered), aspiration should be performed inside the CPB circuit.
8. The collection, concentration, and washing procedures are performed according to the user manual.
9. After washing, the blood is returned to the dedicated bag and transfused to the patient using a blood transfusion filter.

### **Settings for Cell Saver Elite**

Bowl size: 225mL

Suction pressure: "Smart Suction" mode

Fat Removal: Off

Automatic washing: ON

Treat the blood before the enrichment of the bowl is completed: ask

Pump Flow Control: ON

Concentrator pump flow: 500 mL/h

Minimum cleaning volume: 1000 mL

Washing pump flow rate: 450mL/h

Smart Empty: ON

High-speed mode concentrator pump flow: 800 mL/h

High-speed mode washing pump flow rate: 800 mL/h

## **Control Product**

### **Name, Content, etc.**

Allogeneic RBC transfusion

### **Packaging and Labeling**

Contained in a bag visually distinct from the dedicated salvaged blood transfusion bag.

### **Quality Control**

The samples are stored under refrigeration.

# **Participants**

Eligibility is assessed in two stages: provisional and final registration. Participants who meet all the inclusion criteria and none of the exclusion criteria are considered eligible for each stage.

## **Imnclusion and Exclusion Criteria for Provisional Registration**

Patients who meet all the inclusion criteria and do not meet any of the exclusion criteria are provisionally enrolled.

## **Inclusion Criteria**

1. Patients with consent from the patient
2. Patients ≥ 40 years of age at the time of obtaining consent
3. Patients who use a heart-lung machine and undergo cardiovascular surgery using a median sternotomy approach on an elective basis (surgery application was made by 24 o'clock the day before the surgery date)
4. Patients who fall under any of the following (fall under the case of high risk of bleeding)
   1. Resumption thoracic surgery with a history of cardiac large vessel surgery with a median sternotomy approach in the past
   2. Patients undergoing aortic base surgery (Ross surgery, aortic valve replacement with annular enlargement, aortic base replacement), ascending aortic replacement, or arch aortic replacement
   3. Patients undergoing valvular disease surgery of 2 or more valves, except tricuspid annuloplasty
   4. Patients who undergo CABG combined with valvular disease surgery excluding tricuspid annuloplasty

## **Exclusion Criteria**

1. Patients undergoing descending aortic replacement, thoracoabdominal aortic replacement, heart transplantation, ventricular assist device transplantation, or pulmonary valve replacement
2. Extremely high risk of bleeding, defined as patients with three or more prior cardiovascular surgeries via median sternotomy. For other cases in which the bleeding risk is considered to be extremely high, the final decision on exclusion will be made through discussion between the surgeon and the anesthesiologist.
3. Patients who do not comply with the preoperative antiplatelet or anticoagulant withdrawal period (see Table 1)
4. Patients with active bacterial or viral infections
5. Pregnant or lactating patients
6. RhD antigen-negative patients
7. If the patient has clinically significant irregular antibodies, or has a history of clinically significant irregular antibodies in the past, and the availability of the relevant irregular antibody-negative blood products is limited (the presence or absence of clinical significance is determined by the " [Guidelines for red blood cell typing (erythrocyte testing), 4th edition (revised)]" [18]) Judge with reference to)
8. Patients for whom the principal investigator or co-investigator deems them inappropriate to participate in this study for any other reason

Table 1: Preoperative antiplatelet or anticoagulant withdrawal period

| Generic name | Withdrawal period |
| --- | --- |
| Antiplatelet agents | |
| Aspirin | 7 days |
| Clopidogrel | 5 days |
| Prasugrel | 7 days |
| Ticlopidine | 7 days |
| Ticagrerol | 3 days |
| Cilostazol | 3 days |
| Anticoagulants | |
| Warfarin | 3 days |
| Dabigatran | 3 days |
| Rivaroxaban | 3 days |
| Apixaban | 3 days |
| Edoxaban | 3 days |

＊For drugs with a discontinuation period of x days, fulfillment of the prescribed discontinuation period is defined as having elapsed more than x days (i.e., x × 24 hours) from the time of the last administration.

## **Rationale for Criteria**

### **Rationale for Inclusion Criteria**

1): Written consent is required as this is an interventional study

2–4) To identify patients suitable for inclusion in this trial based on the study's target population

### **Rationale for Exclusion Criteria**

1–3, 5) To ensure accurate evaluation of the study treatment
4, 6–8) To ensure participant safety

## **Selection and Exclusion Criteria for Registration**

Provisionally registered cases are registered after confirming that they meet the following inclusion criteria and do not conflict with the exclusion criteria.

## **Criterias of choice**

Patients who underwent allogeneic RBC transfusion in a heart-lung machine

## **Exclusion Criteria**

1. If the withdrawal period for antiplatelet or anticoagulants (see Table 1) was not complied with between the time of provisional registration and the date of surgery.
2. If the surgical procedure changes between the date of provisional registration and the date of surgery, or during surgery, and conflicts with the selection criteria for provisional registration, or meets any exclusion criteria for provisional registration.

## **Rationale for Criteria**

### **Rationale for Inclusion Criteria**

If this criterion is not met, surgery may proceed without transfusion, making the case outside the high-risk population targeted by this study. Bloodless surgery refers to a procedure in which anemia is corrected solely with salvaged RBC without the need for allogeneic RBC transfusion. This is only feasible when the blood loss is minimal.

### **Rationale for Exclusion Criteria**

Set to ensure valid evaluation of study treatment effects

# **Study Procedures**

## **Informed Consent**

### **Voluntary Participation**

This clinical study is conducted in accordance with the ethical principles of the Declaration of Helsinki and the Ethical Guidelines for Life Science and Medical Research Involving Human Subjects. Participation in this study is voluntary, and respect for the fundamental human rights of participants is maintained. Patients will receive appropriate medical care, regardless of whether they choose to participate in this study. The study will be fully explained to the participants using an explanatory document, and written informed consent will be obtained.

### **Procedure for Obtaining Informed Consent**

The principal investigator or sub-investigator explains the study using an explanatory document, provide sufficient time for consideration, and obtains written consent based on the participant’s free will.

When obtaining written consent, the participant must fully understand the content and sign and date the consent form. The investigator who provided the explanation also signs and dates this form.

### **Re-Consent**

If the study protocol is amended in a way that may affect the participant’s decision to continue the study, the revised explanatory document and consent form are approved by the ethics committee. Thereafter, the new content is explained to the participants, and re-consent is obtained in writing.

### **Withdrawal of Consent**

Participants may withdraw their consent at any time, without penalty. However, data already used in published research cannot be withdrawn. In cases where withdrawal is difficult owing to unforeseen circumstances, the matter is referred to the ethics committee for approval.

After withdrawal, no further data is collected, and any unused samples and data is not used in the future. The explanatory document includes information on the ability to withdraw, potential limitations, reasons, and contact information. When a participant expresses an intent to withdraw, it is recorded in the withdrawal form or medical record, and appropriate action is taken. If withdrawal is not possible, a clear explanation is provided to the participant to seek their understanding.

## **Provisional Registration**

The principal or sub-investigator obtains consent from the participant and verify that they meet the provisional registration inclusion criteria and do not meet any of the exclusion criteria. An identification number is then issued. If the patient does not meet the criteria, screening will end and regular medical care will be provided. The reason for ineligibility must be recorded in the screening logs.

Once the target sample size (142 final registrations) is reached, consent acquisition is temporarily suspended and resumed only if additional cases are required.

## **Final Registration**

Participants who meet the inclusion criteria and do not meet the exclusion criteria at the time of final registration are formally registered. Those deemed ineligible at this stage exit the study and receive standard medical care. In such cases, participants are informed of their ineligibility after surgery.

## **Randomization and Blinding**

After final registration, the principal or sub-investigator accesses the web-based system to input the required information for randomization. Participants are assigned in a 1:1 ratio to either the salvaged RBC group or the allogeneic RBC group using the stratified block randomization method.

Stratification factors include whether the surgery involves aortic arch replacement with antegrade cerebral perfusion and age (40–64 vs. 65 and older).

The study is single-blind: participants, outcome assessors, surgeons, surgical assistants, and physicians responsible for postoperative care remain blinded to the group assignments. Only the anesthesiologist involved in the procedure is unmasked. Blinding may be lifted by postoperative physicians in cases of uncontrollable bleeding that require knowledge of the assigned group..

## **Administration of the Study Treatment**

Consent and provisional registration are completed before the day of surgery. The final registration and randomization occurs during CPB. From the point of CPB weaning (protamine administration), the study product is administered based on the hemoglobin levels.

< Administration criteria for the study treatment>

If hemoglobin is less than 10.0 g/dL or is anticipated to drop below this level, transfusion is administered per group assignment.

### **Salvaged RBC Group (Investigational Product Group)**

From weaning off CPB until exiting the operating room, salvaged RBC is administered preferentially over allogeneic RBC to treat anemia. Residual blood in the CPB circuit (post-CPB blood) is collected immediately after the removal of the arterial and venous cannulas using the cell salvage device. If anemia is not corrected after administering all available salvaged RBC or if correction is not expected, allogeneic RBC is transfused.

If salvaged RBC become available during the transfusion of allogeneic RBC, the transfusion of allogeneic RBC is suspended and replaced with salvaged RBC. If salvaged RBC is unavailable when needed, allogeneic RBC is used.

After recovering the post-CPB blood, a 2 mL sample of the first returned salvaged RBC is collected and sent to an external laboratory to measure the heparin concentration.

After ICU admission, allogeneic RBC is used for the treatment of anemia.

### **Allogeneic RBC Group (Control Product Group)**

From CPB weaning until operating room exit, anemia is treated exclusively with allogeneic RBC without using salvaged RBC.

Residual blood in the CPB circuit (post-CPB blood) is still collected using the cell salvage device after removing the cannulas. However, the salvaged RBC is not transfused to the patient.

### **Criteria for Discontinuation of Study Treatment**

- In Salvaged RBC group, if purulent material or contamination from patient infection is observed in salvaged RBC, and its use may result in new infections
- In allogeneic RBC Group, if allogeneic RBC are insufficient and the surgeon or anesthesiologist determines that salvaged RBC is essential to avoid life-threatening anemia
- If unforeseen intraoperative complications require a change to a very high-risk surgical procedure
- If mechanical circulatory support becomes necessary during surgery
- If the principal investigator or sub-investigator deems continuation of study treatment to be difficult

## **Pre- and Concomintant Treatments**

### **Pre-Treatment Defined by the Study**

- Antithrombin III (Neuart®): If the ACT does not exceed 400 s after the administration of 300–500 U/kg of heparin before CPB initiation, administer 500–1500 U of antithrombin III.
- Prothrombin Complex Concentrate (Kcentra®): If PT-INR exceeds the upper limit of normal on the day of surgery despite appropriate warfarin withdrawal, administer 500–1000 U before surgery begins.

### **Concomintant Therapies**

- FFP: Begin after weaning from CPB. The ratio of FFP to total RBC transfusion volume (salvaged + allogeneic) should not exceed 1:1. If the fibrinogen level is ≥200 mg/dL and there is no bleeding tendency, FFP transfusion should not be administered.
- Cryoprecipitate: If fibrinogen is <100 mg/dL, administer the equivalent of 12 units of FFP. Consider 12 units of FFP if the fibrinogen level is 100–149 mg/dL.
- Tranexamic Acid: Administer a 1 g bolus at the start of surgery, followed by continuous infusion at 2 mg/kg/h until the end of surgery.
- Protamine: Administer 3 mg/kg at CPB weaning. If the clotting time ratio in a blood viscoelastic test (Quantra) is ≥1.2 or ACT exceeds H-ACT (ACT after heparin neutralization), additional doses are required.
- Voluven® (Colloid Solution): Limit the total intraoperative volume to 50 mL/kg.

### **Post-Treatment**

Within the first 12 hours after ICU admission, the transfusion protocols are as follows:

- RBC Transfusion: Administer allogeneic RBC if hemoglobin level is <10.0 g/dL or is expected to fall below this level. Leftover salvaged RBC should not be transfused. During re-thoracotomy within 12 hours, only allogeneic RBC is used for both groups. After 12 hours, there are no restrictions on the use of salvaged or allogeneic RBC during surgery.
- Platelet Transfusion: Administer if the platelet count is <100,000/μL and clinical bleeding is evident.
- FFP Transfusion: Administer if there is a bleeding tendency with APTT > 50 seconds, PT-INR > 1.3, or fibrinogen < 150 mg/dL. However, if the clotting time ratio is ≥ 1.2, protamine is administered, and the APTT value is reassessed thereafter. In cases of massive bleeding, transfusion is performed in the ICU with a target ratio of total FFP transfusion volume to total allogeneic RBC transfusion volume of approximately 1.
- Protamine: Administered if clotting time ratio ≥1.2 in the Quantra test or if ACT exceeds H-ACT.

## **Discontinuation Criteria and Procedures for Study Treatment**

### **Procedures for Discontinuation of Study Treatment**

If any discontinuation criteria are met, the principal or sub-investigator stops the administration of the investigational product. The date and reason for discontinuation are recorded in the medical charts. Data collection of the predefined observation items continues until the end of the study, even if the study treatment is discontinued. If discontinuation is due to an adverse event deemed likely to be caused by the study treatment, appropriate procedures are followed according to the adverse event reporting policy.

## **Discontinuation Criteria and Procedures for Study Participation**

### **Discontinuation Criteria**

If, for any of the following reasons, the subject is unable to complete the study or must discontinue the administration of the study formulation, the principal investigator (or co-investigator) terminates the subject's participation in the study.

1. The participant requests to withdraw from the study
2. Surgery is cancelled after consent has been obtained
3. For safety reasons, the principal investigator deems it necessary to discontinue participation
4. The study itself is terminated
5. Other reasons determined by the principal or sub-investigator

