## **When the study is stopped early (date of decision to discontinue+3)**

The following observations and tests are performed within three days of study discontinuation.

| 1) Study Treatment Information | |
| --- | --- |
| Discontinuation/interruption of treatment | Presence or absence; if applicable, record the date of discontinuation/interruption, reason, and subsequent management. |
| 2) Clinical and Laboratory Data ^*4^ | |
| Laboratory tests | White blood cell count, hemoglobin, platelet count, total protein, albumin, total bilirubin, direct bilirubin, AST, ALT, creatinine, LDH, CK, CK-MB, sodium, potassium, chloride, calcium, CRP, PT-INR, APTT, fibrinogen |
| 3) Adverse Event Information | |
| AEs | Date of onset, event name, known or unknown, seriousness, severity, causal relationship, treatment, outcome, date of outcome confirmation, readmission status (presence or absence), date of readmission, date of discharge, and other relevant details |
| 4) Outcome Information | |
| Survival status | Outcome: alive, deceased, or lost to follow-up  Date of last confirmed survival or date of death; in case of death: cause of death  If lost to follow-up: reason for loss to follow-up |
| Study withdrawal | If applicable, record the date of withdrawal and the reason |

*4 If test results from other visits or routine clinical care are available within one day prior to the date of study discontinuation, those results are used be used.**Observation and Inspection Schedule**

| Survey Period  Survey Items | Test Period | | | | Early discontinuation |
| --- | --- | --- | --- | --- | --- |
|  | Visit 1 | Visit 2 | Visit 3 | Visit 4 |  |
|  | **Consent, eligibility check, provisional registration** | **Final registration, allocation (prior to study treatment initiation)** | **During study treatment** | **End of Exam** |  |
| Stipulated days | -30 days~ | 0 days | 0 days | 30 days | ― |
| Tolerance | ― | ― | +3 days | ± 5 | +3 days |
| **Informmed consent** | ◎ |  |  |  |  |
| **Basic subject information** | ○ |  |  |  |  |
| **Target disease information** | ○ |  |  |  |  |
| **Study treatment information** |  |  | ○ | ○ | ○ |
| **Oral medication information** | ○ | ○ |  |  |  |
| **Physical findings** | ○^※1^ | ○^※2^ | ○ |  |  |
| **Vital signs** |  |  | ○ |  |  |
| **Laboratory tests (complete blood count, biochemistry, blood type-related, coagulation, viscoelastic testing)** | ○^※1^ | ○^※2^ | ○ | ○^※3^ | ○^※4^ |
| **Blood gas analysis** |  |  | ○ |  |  |

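### An investigator-judged treatment stop can fall under two conflicting rules on follow-up, and the early-discontinuation table leaves out the 12-hour drainage that is the primary outcome

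*Protocol*

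**What the plan says.** Five places in the protocol bear on this.

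- **7.5.3 (criteria for stopping study treatment).** The list includes "If mechanical circulatory support becomes necessary during surgery" and ends with an open item: "If the principal investigator or sub-investigator deems continuation of study treatment to be difficult".
- **7.7.1 (procedure after a treatment stop).** "Data collection of the predefined observation items continues until the end of the study, even if the study treatment is discontinued".
- **7.8.1 (criteria for ending participation).** The sentence opens "If, for any of the following reasons, the subject is unable to complete the study", and its full condition is that "the subject is unable to complete the study or must discontinue the administration of the study formulation". In either case the investigator "terminates the subject's participation in the study". The five reasons are the participant's request, cancelled surgery, safety as judged by the principal investigator, termination of the study, and "Other reasons determined by the principal or sub-investigator".
- **7.8.2 (procedure after participation ends).** Data collection is expressly ended only for voluntary withdrawal. Nothing is said for the other reasons.
- **8.4 and 8.5 (visit content).** Chest-tube loss over 12 hours is listed at Visit 4 only. For early discontinuation, "The following observations and tests are performed within three days of study discontinuation". That table holds the details of the stop, laboratory tests, adverse events, survival status and withdrawal. It has no drainage and no transfusion volume.

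**The concern.** Stopping treatment and leaving the study are different events, and the protocol mostly treats them so. Section 7.8.1 blurs the line by naming a treatment stop as one of the situations that ends participation. Where the stop rests on the investigator's judgement, 7.7.1 says to keep collecting and 7.8.1 says to end participation.

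A patient taken out under 7.8.1 moves to the 8.5 table, which does not ask for the primary outcome. Some 7.5.3 triggers describe difficult operations: life-threatening anaemia with too little allogeneic blood, a change to a very high-risk procedure, mechanical circulatory support. It is a reasonable inference, though not one the protocol states, that patients near these situations drain atypical volumes. Under 7.4 the anaesthesiologist knows the allocation and treatment is given in the operating room, so decisions to stop can be made with the arm known.

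A non-inferiority comparison of mean drainage is sensitive to a few missing large values if they go missing more in one arm than in the other. An analysis plan can specify how missing values are handled, but it cannot recover a value that the schedule never asked for.

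**Working it through.** **1. The rules side by side**

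| Situation of a randomised patient | Section that applies | Is 12-hour drainage listed? |
|---|---|---|
| Treatment stopped on a specific 7.5.3 trigger, stays in study | 7.7.1 | Yes, Visit 4 |
| Treatment stopped on investigator judgement (last item of 7.5.3) | 7.7.1, and 7.8.1 if the safety or open reason is used | Yes under 7.7.1; no under 7.8.1 with 8.5 |
| Participation ended by the investigator | 7.8.1, 7.8.2 (silent on data), 8.5 | No |
| Voluntary withdrawal | 7.8.2 | No, by design |

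The conflict is in row 2 and the gap is in row 3.

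**2. The plan's own sample size, for scale**

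Inputs from the Study Overview: margin 200 mL, SD 400 mL, α = 0.025 (taken as one-sided), power 80%, true difference taken as 0.

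- Normal approximation: n = 2 × (1.960 + 0.842)² × 400² / 200² = 2 × 7.85 × 4 = 62.8, so 63 per group.
- With the t distribution: 64 per group (power 0.801), the stated figure.
- Dropout: 128 / 0.9 = 142.2, against 142 stated.

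The figures reproduce. The allowance is 142 − 128 = 14 patients, or 7 per group.

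**3. How far missing large values move one arm's mean**

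Assumption: drainage has mean 674 mL and SD 400 mL (the preliminary data), and the heaviest share of one arm is missing.

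| Heaviest share missing | Fall in mean, lognormal | Fall in mean, normal |
|---|---|---|
| 2% | 32 mL | 20 mL |
| 5% | 61 mL | 43 mL |
| 10% | 99 mL | 78 mL |

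Two of 71 is 2.8% and four of 71 is 5.6%.

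**4. Effect on the false non-inferiority rate**

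Assumptions: lognormal drainage, mean 674 and SD 400 mL in the control arm; the salvage arm shifted up by exactly 200 mL; 71 per arm; complete cases only; pooled t-interval with the upper 97.5% limit compared with 200 mL; 40,000 simulated trials.

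| Patients missing | False non-inferiority rate |
|---|---|
| None | 2.5% |
| Salvage arm only: 2 at random from the top fifth | about 4.4% |
| Salvage arm only: 4 at random from the top fifth | about 8% |
| Salvage arm only: the 2 heaviest | about 9% |
| Both arms: equal random loss from the top fifth | about 2.5% |
| Both arms: the 2 heaviest in each | about 4% (3.7% in one run) |

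Taking exactly the 4 heaviest salvage patients would give about 19%, but that needs perfect selection in one arm and is a worst case. If large values are missing from the control arm only, the control mean falls, the observed difference grows, and the rate drops below 2.5%: the error then runs against non-inferiority.

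The protocol gives no number of patients likely to be affected and no split by arm.

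**The case against.** The natural reading keeps the two tracks apart: stops under 7.5.3 follow 7.7.1, and exits from the study follow 7.8. The opening words of 7.8.1 confine it to five reasons, none of which is a specific 7.5.3 trigger. Section 7.8.2 ends data collection only for voluntary withdrawal. Drainage sits in the ICU and electronic records named in 8.4 and can be retrieved later. Intraoperative transfusion volumes are already collected at Visit 3. Missing-data handling is left to an analysis plan that is not shown.

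Most of this stands, and it rules out two stronger readings.

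- A reader might infer that 7.8.1 removes everyone who stops study treatment. It does not. It reaches a treatment stop only through a listed reason, in practice the safety item or the open item.
- A reader might infer that the heaviest bleeders of the salvage arm will be lost and the trial tilted towards non-inferiority. The protocol does not support that direction. The only arm-specific trigger tied to severe anaemia is in the control arm. The only salvage-specific trigger is contamination of the salvaged blood, which is no marker of bleeding. The rest apply to both arms, and mechanical support is not described as a bleeding event.

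What the objection does not remove is the overlap between two discretionary items, the silence of 7.8.2 on investigator-ended participation, and the absence of drainage from 8.5. That a value can be retrieved does not mean that anyone is told to retrieve it.

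**Conclusion.** The point holds as a conflict and a gap in the rules on data collection. Sections 7.7.1 and 7.8.1 can give opposite instructions for the same investigator-judged treatment stop. A randomised patient whose participation the investigator ends has no listed point at which 12-hour drainage is recorded. The protocol does not order the data to be discarded except after voluntary withdrawal.

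The effect on the result cannot be sized from the document. The rates of about 4–9% with loss confined to the salvage arm rest on an assumed distribution, assumed numbers lost, an assumed arm and an unadjusted complete-case analysis. Balanced loss leaves the rate at about 2.5–4%, and control-arm loss makes a non-inferiority claim harder. They show only that two to four patients can matter against a 200 mL margin, well inside the planned allowance of 7 per group. The correction is worth making because it costs little and closes a route to informative missing data.

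**What to change.** Reconcile 7.5.3, 7.7.1, 7.8.1, 7.8.2 and 8.5 on data collection:

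1. In 7.8.1, delete the alternative that makes having to stop the study formulation a ground for ending participation, so that treatment stops are governed by 7.7.1 alone.
2. In 7.8.2, state that for randomised participants only withdrawal of consent ends outcome collection. In every other case the listed outcomes are still collected.
3. In the 8.5 table, add 12-hour drainage, including blood loss at any re-thoracotomy as section 4.1 requires, and postoperative transfusion volumes.

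The cost is a short protocol amendment and a few case report form fields, filled from routine ICU and electronic records. No treatment rule, visit or sample-size figure changes.
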